### Secondary outcomes:

Change in intestinal inflammatory markers between the placebo and protein supplement group (group E vs group B).Changes in GM composition and intestinal inflammatory markers between other treatment groups (group A vs group E; group C vs group E; group D vs group E).Associations between baseline GM composition and change in intestinal inflammation or sarcopenia-defining parameters.

### Assessment of GM composition and statistical analyses

GM analyses will comprise determination of within sample diversity (α-diversity), including sample richness, taxa abundance, evenness, and taxa distribution through the following indices: Chao 1, Shannon and Simpson’s indices, abundance-based coverage estimators (ACE) index and the Good’s Coverage index. Taxa abundance will be expressed as Operational Taxonomic Units (OTU) and/or Amplicon Sequence Variants (ASV). Sequencing reads will be demultiplexed with LotuS (version 1.565) and processed further with the DADA2 pipeline (version 1.6.0), using the RDP classifier version 2.12 for taxonomy assignment (default parameters). Between sample dissimilarity (β-diversity) will be determined with Bray–Curtis dissimilarity (through a distance based non-parametrical permutational analysis of variance (PERMANOVA) test) and weighted and unweighted UniFrac (through principal coordinates analysis (PCoA)), respectively. Comparisons of relative GM abundance between sarcopenic and non-sarcopenic older adults will be performed through linear discriminant analysis (LDA) effect size (LEfSe). GM analyses, as well as visualization of the results will be performed using R vegan and phyloseq packages [54]. Enterotyping (or community-typing) will be performed based on the Dirichlet-multi-nominal Model (DMM) approach in R (dmn function) as previously described on a combined genus-level abundance matric containing the study samples as well as 1106 Flemish Gut Flora Project (FGFP) samples to increase accuracy [55, 56]. Continuous data will be checked for normality with the Shapiro–Wilk test. The t-test will be performed for between-group analysis of continuous clinical parameters, if normally distributed. For GM analyses, non-parametric testing will be applied. The Mann–Whitney U test will be performed in case of non-parametric distribution. Correlations between microbiota species and clinical parameters will be assessed with Spearman correlation. Linear regression models adjusted for putative confounders (e.g., age) will be used to check for associations between GM species abundance and clinical parameters. To determine possible effects of the interventions on GM in different groups, linear mixed models will be applied. Multiple testing corrections will be applied if it is applicable (Benjamini-Hochberg- False Discovery Rate (FDR)). An FDR of ≤ 0.10 will be taken into account for GM analyses [57]. Level of significance will be a p-value of ≤ 0.05. A bioinformatician from VIB and a statistician from LBiostat will be consulted for the statistical analyses.

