#### Baseline test visit

For both the non-sarcopenic controls and the sarcopenic participants, a test visit at the study center will follow the preparation period. During this visit, the four-day food diary, the IMU and the two frozen fecal samples brought along by the participant (avoiding thawing using ice packs) will be collected and fasted blood samples will be taken.The fecal samples will immediately be stored at -80 °C until analysis of intestinal inflammatory markers (fecal calprotectin, lactoferrin and S100A12) and GM composition. Quantitative Microbiome Profiles (QMP) will be obtained through the following extensive -omics analysis. Targeted (16S/18S) amplicon sequencing analysis of the V3-V4 variable region of the 16S rRNA gene, via reverse polymerase chain reaction (RT-qPCR) technique will provide information about GM taxonomic composition, i.e., the type of GM present, and their abundance.. Metagenomic analysis (comprehensive assessment of DNA of the complete content of a clinical sample) will be performed through whole genome shotgun analysis using next generation platforms. Intestinal inflammatory markers will be determined through Enzyme Linked Immunosorbent Assay (ELISA).In fasted blood samples, the following parameters will be determined: systemic inflammatory parameters (hs-CRP, IL-4, IL-6, IL-13, IL-1β, TNF-α and creatine kinase), muscle markers (myostatin, activin A, irisin, apelin), clinical parameters (hemoglobin, eGFR, serum albumin, fasting glucose, red blood cell count, hematocrit, Mean Corpuscular Volume (MCV), Mean Corpuscular Hemoglobin (MCH), Mean Corpuscular Hemoglobin Concentration (MCHC), white blood cell count and formula, platelet count, hemoglobin A1c (HbA1c), ferritin, aspartate aminotransferase (AST), alanin transaminase (ALT), γ-glutamyltransferase, total and direct bilirubin, total protein, serum protein electrophoresis, uric acid, sedimentation rate, triglycerides and total, high-density lipoprotein (HDL) and low-density lipoprotein (LDL) cholesterol, and hormonal status (25-hydroxyvitamin D, vitamin B12, morning cortisol, insulin, insulin-like growth factor (IGF-1)).

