### Outcome measurements

For the cross-sectional phase, outcome measurements will be taken at the baseline test visit.The primary outcomes in this phase are:Differences in multiple GM α-, and β-diversity indices, enterotypes, bacterial cell counts and abundance of specific taxa between sarcopenic older adults and non-sarcopenic controls using two fecal samples collected in each group at the baseline test visit [52, 53]. Both GM diversity indices and measures for expression of bacterial abundance will be specified in the section “Assessment of GM composition and statistical analyses” further below.Differences in the levels of the intestinal inflammatory markers fecal calprotectin, lactoferrin and S100A12 between sarcopenic older adults and non-sarcopenic controls using two fecal samples collected in each group at the baseline test visit.Secondary outcomes assessed in sarcopenic older adults are:Associations between GM composition and clinical parameters: 1) ALM (by whole body DXA and BIA), muscle strength (HGS, CST and knee strength) and physical performance (gait speed and SPPB); 2) protein intake by four-day food diaries and risk of malnutrition by the MNA-SF.Associations between GM and levels of systemic (hs-CRP; IL4, IL6, IL-13, IL-1β, TNF-α, and creatin kinase) and intestinal (fecal calprotectin, lactoferrin and S100A12) inflammatory markers.Associations between levels of systemic and intestinal inflammatory markers.Associations between fecal calprotectin, lactoferrin, S100 and respectively: 1) aforementioned systemic inflammatory markers; 2) ALM (whole-body DXA), muscle strength (HGS, CST, knee strength) and physical performance (gait speed, SPPB); 3) systemic muscle biomarkers (myostatin, activin A, irisin, apelin).

For the longitudinal phase in sarcopenic participants, outcome measurements will be collected from the baseline test visit until the week 12 visit. The primary outcome of this phase is:Change in GM composition between the protein intervention group (group B, Fig. 3) and the placebo group (group E).

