## Discussion

TEMPUS-FUGIT aims to unravel the gut-muscle axis in sarcopenia by a two-fold set-up. First, cross-sectionally, by comparing GM composition and intestinal inflammation between sarcopenic and non-sarcopenic older adults. Second, in a longitudinal RCT set-up, by assessing the effects of combined, optimized, and individualized anabolic treatments for sarcopenia on GM and intestinal inflammation in sarcopenic older adults.

A first strength of TEMPUS-FUGIT is its well-considered design, defining sarcopenia according to the most recent criteria of the EWGSOP 2 [30]. Moreover, this study excludes participants with comorbidities influencing GM (e.g., malignancy, IBS, IBD or chronic kidney disease) and medications influencing muscle (e.g. corticoids or diabetes medications), resulting in an ideal population to explore the gut-muscle axis. Furthermore, this study aims to match both groups according to gender, age and BMI, since these factors influence both GM composition and sarcopenia [18, 60]. Thus, TEMPUS-FUGIT avoids bias related to these parameters, which was not always the case in previous studies investigating muscle mass, strength and GM in older adults [61–63].

Secondly, state-of the art metagenomic sequencing methods (e.g. Quantitative Microbiome Profiling, Shotgun whole genome sequencing) will be used to explore quantitative signals and bacterial functionality, which has not yet been done in an EWGSOP2-defined sarcopenic population [17].

Third, rather than solely comparing GM between non-sarcopenic and sarcopenic older individuals, TEMPUS-FUGIT pioneers in the assessment of intestinal inflammation markers, i.e., S100A12, fecal lactoferrin and fecal calprotectin, with the latter marker having a high specificity and sensitivity for gut inflammation [64]. This study will also investigate the possible associations between intestinal inflammation and respectively systemic inflammation and GM composition and its contribution to the development of sarcopenia, which has, to our knowledge, not yet been investigated.

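### The only method named specifically for comparing taxa between cases and controls is LEfSe on relative abundance, which uses no total-load information and is not tied to the stated FDR of 0.10

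*Protocol article*

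**What the plan says.** All references are to the Protocol article.

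- **Outcomes.** *Outcome measurements* includes among the primary cross-sectional outcomes differences in "enterotypes, bacterial cell counts and abundance of specific taxa between sarcopenic older adults and non-sarcopenic controls". It defers the choice of abundance measure to the analysis section.
- **Data.** *Baseline test visit*: "Quantitative Microbiome Profiles (QMP) will be obtained through the following extensive -omics analysis". The *Discussion* counts these methods as a strength because they "will be used to explore quantitative signals and bacterial functionality".
- **Taxon comparison.** *Assessment of GM composition and statistical analyses*: "Comparisons of relative GM abundance between sarcopenic and non-sarcopenic older adults will be performed through linear discriminant analysis (LDA) effect size (LEfSe"). The same section expresses abundance as OTUs or ASVs and never mentions a cell-count scale.
- **Other testing.** The section also says "For GM analyses, non-parametric testing will be applied" and names the Mann–Whitney U test. Regression with confounder adjustment is assigned to relating taxa to clinical measures, not to the group contrast.
- **Error rate.** "Multiple testing corrections will be applied if it is applicable (Benjamini-Hochberg- False Discovery Rate (FDR")), then "An FDR of ≤ 0.10 will be taken into account for GM analyses", then "Level of significance will be a p-value of ≤ 0.05".
- **Design.** *Participants*: groups are matched on gender, with calipers for age and BMI. *Preparation period*: stool consistency is scored on the Bristol chart for each sample.

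**The concern.** Three things do not fit together.

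1. **Scale.** Proportions sum to one, so a rise in one taxon pushes the others down, and a change in total load shared by all taxa disappears. The study obtains profiles that would separate these cases, but the method named for taxa is not applied to them.
2. **Error rate.** LEfSe as commonly run passes a taxon that clears an unadjusted rank test and then an LDA-score cut-off. Nothing in the text says that its screening p-values go through Benjamini–Hochberg, so its list need not have an FDR of 0.10.
3. **Adjustment.** LEfSe takes a class and an optional subclass. It does not use matched sets or covariates, so stool consistency, which is recorded but not matched, cannot enter.

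The study hopes to contribute microbial biomarkers of sarcopenia. A taxon could be put forward when its absolute number does not differ, or a real shift in load could be missed at taxon level, and readers would assume an error rate that the named procedure may not deliver.

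**Working it through.** **Can the plan's figure be reproduced?** No. The FDR of 0.10 is a target. The article gives no number of taxa, share of true differences, LEfSe alpha or LDA cut-off. What follows uses stated assumptions and the planned 100 per group.

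**1. Scale, by arithmetic.** Let a genus hold share s of cells and double, with all else unchanged. Total cells become 1 + s, so every other genus changes in proportion by 1/(1 + s) − 1:

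| s | apparent change in every other genus |
|---|---|
| 0.10 | 1/1.10 − 1 = −9.1% |
| 0.20 | 1/1.20 − 1 = −16.7% |
| 0.30 | 1/1.30 − 1 = −23.1% |
| 0.40 | 1/1.40 − 1 = −28.6% |

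**2. Unadjusted screen, no true differences.** Expected false passes = m × 0.05. Under independence, P(at least one) = 1 − 0.95^m.

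| m taxa | expected false passes | P(at least one) |
|---|---|---|
| 50 | 2.5 | 0.92 |
| 100 | 5 | 0.994 |
| 200 | 10 | >0.999 |
| 500 | 25 | >0.999 |

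**3. Unadjusted screen, some true differences.** Assumptions: standardised difference 0.5, independent tests, rank-test efficiency 0.955. The mean of the test statistic is 0.5 × √(50 × 0.955) = 3.46, which gives power of about 0.93 at two-sided 0.05. Hand check with 100 taxa, 5 truly different: false 95 × 0.05 = 4.75, true 5 × 0.93 = 4.65, ratio 4.75/9.40 = 0.51. Simulation (2,000 runs per setting, 50 to 500 taxa):

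| truly different | FDR, p ≤ 0.05 | FDR, BH at 0.10 | power, p ≤ 0.05 | power, BH |
|---|---|---|---|---|
| 5% | 0.48–0.51 | 0.09–0.11 | 0.93 | 0.71–0.72 |
| 10% | 0.30–0.32 | 0.09 | 0.93 | 0.80 |
| 20% | 0.16–0.18 | 0.08 | 0.93 | 0.86–0.87 |

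The excess of BH over 0.10 is simulation error.

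**4. LDA filter and scale together.** This used a simplified LEfSe: rank test at 0.05 plus LDA score > 2, computed one taxon at a time without bootstrap. There were 100 taxa, 100 per group and 100 runs. Mean number of taxa flagged:

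| scenario | LEfSe-type, relative | BH 0.10, relative | BH 0.10, absolute |
|---|---|---|---|
| no difference | 4.7 (5.2 before the LDA filter) | 0.1 | 0.1 |
| total load halved in cases | 4.2 | 0.2 | 99.9 |
| one dominant taxon doubled | 13.6 | 4.6 | 1.2 |

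The last two columns share the same multiplicity rule, so they isolate the effect of scale. The first two share the same scale, so they isolate the effect of the flagging rule. In these settings the LDA filter removed few false passes.

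**The case against.** Several stronger readings are tempting, and the text does not support them.

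- *LEfSe is the only between-group test.* The general sentences on non-parametric testing, Mann–Whitney and Benjamini–Hochberg apply to microbiota analyses and could cover taxa on a quantitative scale. They state no scale, however, and LEfSe remains the only method named specifically for taxa.
- *The quantitative profiles are discarded.* Cell counts are a separate primary outcome, so total load would still be compared between groups. The loss is confined to the taxon comparison.
- *Age, sex and BMI are uncontrolled.* They are handled by matching. What stands is that LEfSe ignores the matched sets, that calipers leave some residual difference, and that stool consistency is neither matched nor adjusted for.
- *The 0.10 rate is certain to fail.* That assumes an uncorrected screen. The text neither states nor rules this out, and Benjamini–Hochberg could be applied to the screening p-values.

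Two further points are fair. A fall in proportion is not the same as a flagged taxon: with one dominant taxon doubled, 13.6 of 100 were flagged, against about 5 expected by chance. Also, the study is declared exploratory, will consult a bioinformatician and a statistician, and may hold LEfSe settings in a fuller document. That excuses missing settings. It does not reconcile a named relative-abundance method with outcomes and strengths described in quantitative terms, or with a stated error rate to which it is not linked.

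**Conclusion.** The point holds for the taxon comparison and should be fixed; it does not invalidate the study. The one method assigned specifically to that comparison does not use the total-load information that the study obtains, and it is not linked to the FDR that the same section sets. The proportion arithmetic (apparent falls of 9.1% to 28.6%) follows for any genus with the assumed share. The error-rate figures (about 5 null passes per 100 taxa; FDR 0.16 to 0.51 against a target of 0.10) hold only if LEfSe is run with an unadjusted 0.05 screen. They also rest on the assumed number of taxa, share of true differences, effect size and independence. The simulated LEfSe was a simplification. The covariate limb reduces to stool consistency and the unused matching.

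**What to change.** In *Assessment of GM composition and statistical analyses*:

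1. Make the primary case–control taxon comparison a per-taxon test on cell-count-scaled abundance, on a rank or log scale, with group and the matching variables (gender, age, BMI) in the model.
2. Apply Benjamini–Hochberg at 0.10 across all taxa tested, and say that this rule, not the general 0.05 level, decides which taxa are reported.
3. Add a sensitivity analysis adjusting for Bristol score. It belongs there because stool consistency may be part of the pathway under study as well as a confounder.
4. Keep LEfSe on relative abundance as a descriptive display, labelled as not FDR-controlled unless a correction is specified.

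The cost is wording; the data are already planned. Fewer taxa will be flagged, and per-taxon power falls, under the assumptions above, from 0.93 to between 0.71 and 0.87 at a standardised difference of 0.5.

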**Methods:**

First, in a cross-sectional case–control phase, 100 community-dwelling adults without sarcopenia will be compared to 100 community-dwelling adults (≥ 65 years) with sarcopenia of similar age-, gender and BMI-ratio, participating in the ongoing ‘Exercise and Nutrition for Healthy AgeiNg’ (ENHANce; NCT03649698) study. Sarcopenia is diagnosed according to the European Working Group on Sarcopenia in Older People 2 (EWGSOP2) criteria. GM composition and intestinal inflammatory markers (fecal calprotectin, lactoferrin and S100A12) will be determined in fecal samples. Systemic inflammatory markers (hs-CRP, IL-4, IL-6, TNF-α, IL-13, IL-1β and creatine kinase) will be determined in fasted blood samples. Both groups will be compared using appropriate statistical testing, whereas linear regression will be used for cross-sectional associations between gut, inflammatory and sarcopenia parameters.

Second, in the longitudinal phase, sarcopenic older adults will be requested to deliver five fecal samples during the 12-week intervention to assess the effects of protein, omega-3 and a physical exercise program on the GM.

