### Participants

In TEMPUS-FUGIT 100 healthy community-dwelling non-sarcopenic older adults (aged ≥ 65 years) will be recruited to be compared with 100 older adults with sarcopenia defined according to the revised definition of the European Working Group on Sarcopenia in Older People (EWGSOP2) [30]. The sarcopenic older adults will also participate in the longitudinal (interventional) phase of the study.

The sarcopenic and the non-sarcopenic group will be gender-matched, whereas for age and Body Mass Index (BMI), caliper matching (maximum tolerated difference between matched persons) will be applied [31]. Sarcopenic older adults will be recruited from the ongoing triple blinded RCT ‘Exercise and Nutrition for Healthy AgeiNg’ (ENHANce) study (Clinical Trial number NCT 03649698) [29]. Participants will be recruited from the environment of Leuven, Flanders, Belgium. To ensure recruitment of a sufficient number of study persons, contacts have been established with the geriatric outpatient clinic (including falls prevention clinic) and representatives of service flats and day care centers or organizations for older adults. Furthermore, medical staff collaborating to the project will use their network for recruitment. Also health care specialists, i.e., general practitioners, pharmacists and physiotherapists will be requested to refer patients who may be eligible for this study. Also information about the study will be distributed by organizations and websites that target older persons, advertisements in local newspapers and distributions of flyers. Older adults, who were initially screened for the ENHANce study but failed to meet the inclusion criteria for sarcopenia, will be re-contacted to participate in the non-sarcopenic control group of the TEMPUS-FUGIT study.

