
### Sample size

In TEMPUS-FUGIT, a pragmatic sample of 100 sarcopenic people from the longitudinal phase, will be compared with 100 non-sarcopenic volunteers. Therefore, 110 non-sarcopenic controls will be recruited, in order to ensure 100 included control persons that, similarly to the sarcopenic participants, have a protein intake < 1.5 g/kg BW/day. Indeed, based on previous similar data, we expect, a drop-out of 5.88% in the non-sarcopenic control group due to a protein intake > 1.5 g/kg BW/day, [58]. Due to the exploratory character of this study, no sample size calculation was performed. Based on previous studies, 100 participants in each group is considered as sufficient for this study [16, 18, 29].

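### Cases and controls are matched on sex, age and BMI, but the tests named for the primary gut-microbiota contrast use neither the pairs nor the matching factors

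*Protocol article*

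**What the plan says.** **Design.** Under Participants: "The sarcopenic and the non-sarcopenic group will be gender-matched, whereas for age and Body Mass Index (BMI), caliper matching" will be used, and the caliper is explained as the "maximum tolerated difference between matched persons". That describes person-to-person matching. The Abstract words it differently: the groups are to be "of similar age-, gender and BMI-ratio", which reads as similarity of the groups as a whole. Caliper widths are not given. The Discussion justifies the matching "since these factors influence both GM composition and sarcopenia" and concludes that bias from these factors is thereby avoided.

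**Size.** Under Sample size, "a pragmatic sample of 100 sarcopenic people from the longitudinal phase, will be compared with 100 non-sarcopenic volunteers". No power calculation was made.

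**Analysis.** Under Assessment of GM composition and statistical analyses:
- The microbiota outcomes get a general rule: "For GM analyses, non-parametric testing will be applied".
- Bray–Curtis dissimilarity is tested by PERMANOVA, and relative abundance in the two groups is compared by LEfSe.
- The rank test named for non-normal data is an unpaired one: "The Mann–Whitney U test will be performed in case of non-parametric distribution".
- A t-test is named only for normally distributed clinical measures, without saying whether it is paired.
- Linear regression adjusted for putative confounders, with age as the example, is stated for GM species abundance against clinical parameters.

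The Abstract makes the same split: testing for the group comparison, regression for the associations.

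**The concern.** The stated analysis of the cross-sectional primary outcomes does not follow the stated design. Two separate things are at stake.

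1. **Precision.** If matching works, the two members of a pair resemble each other on any outcome that depends on sex, age or BMI. An independent-samples test such as Mann–Whitney U treats them as unrelated and so overstates the variance of the group difference. The study pays for matching in recruitment and does not collect the gain.
2. **Residual confounding.** A caliper permits differences up to its width. If cases tend to be older, or differ in BMI, within the tolerated range, that difference passes into an unadjusted contrast.

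The article itself says these factors affect both sides of the comparison, so leaving them out of the contrast is hard to defend when they are measured in everyone.

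**Working it through.** **A figure of the plan's own.** The only derived figure is the 110 controls to recruit: 100 / (1 − 0.0588) = 106.2, so 107 would suffice and 110 is slightly generous. It has no bearing on this point. The article gives no effect size, SD or power to reproduce.

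**Inputs.** From the article: 100 per group, significance level 0.05 (taken as two-sided). Assumed, because the article gives none: within-pair correlation ρ, a true difference of 0.35 SD, and the imbalance and slope used in step 3.

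**Step 1: size of an unpaired test on matched pairs.** The SE that the test assumes is √(2/100) = 0.141 SD. The true SE is √(2(1 − ρ)/100). The actual two-sided size is therefore 2Φ(−1.96/√(1 − ρ)).

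**Step 2: power at 0.35 SD.** 0.35/0.1414 = 2.475.
- Unpaired: Φ((2.475 − 1.96)/√(1 − ρ)).
- Paired: Φ(2.475/√(1 − ρ) − 1.96).

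| ρ (assumed) | SE too large by a factor of | True size of nominal 5% test | Power, unpaired | Power, paired |
|---|---|---|---|---|
| 0 | 1.00 | 5.0% | 70% | 70% |
| 0.05 | 1.03 | 4.4% | 70% | 72% |
| 0.1 | 1.05 | 3.9% | 71% | 74% |
| 0.2 | 1.12 | 2.8% | 72% | 79% |
| 0.3 | 1.20 | 1.9% | 73% | 84% |

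These are normal-theory figures. A simulation of 100 pairs with lognormal outcomes (8,000 runs) agrees for the rank test: Mann–Whitney size is 3.9%, 3.2% and 2.0% at ρ = 0.1, 0.2 and 0.3, while the signed-rank test on log differences stays between 4.5% and 5.2%.

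**Step 3: differences left inside the calipers.** Bias in SD units = covariate imbalance (SD) × standardized slope of the outcome on the covariate. The false-positive rate uses SE 0.141.
- Imbalance 0.2 SD, slope 0.2: bias 0.04 SD, false positives 5.9%.
- Imbalance 0.2 SD, slope 0.3: bias 0.06 SD, 7.1%.
- Imbalance 0.3 SD, slope 0.3: bias 0.09 SD, 9.8%.

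The mean imbalance cannot exceed the caliper divided by the SD. With an assumed age SD of 6 years and a caliper of ±2 years, the ceiling is 2/6 = 0.33 SD. Larger effects need wider calipers, and the article does not state the width.

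**Step 4: what is available.** Sex, age and BMI are known for every participant. Bristol score and food-diary intake are also collected in both groups, because controls follow the same preparation period apart from the interventions.

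**The case against.** **The article is condensed.** It names PERMANOVA and LEfSe without a model formula, promises appropriate testing and says a statistician will be consulted, so terms could appear in a fuller document. This stands in part: silence on PERMANOVA terms does not prove that none will be used. But Mann–Whitney U is by definition an independent-samples test, and adjustment is explicitly attached to a different analysis. Followed as written, the text ignores the matching.

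**Pairs may not exist.** The Abstract's wording fits frequency matching, and then there are no pairs to honour and the loss in precision is negligible. This stands, and it is why the precision figures are conditional. The matching factors would still belong in the model.

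**The correlation may be small.** With close matching, ρ = 0.3 would require sex, age and BMI to explain roughly 30% of the outcome variance, and nothing in the article supports that. At 0.1 the cost is about 3 to 4 points of power. This stands.

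**Some covariates are handled by design.** Included controls must have protein intake below 1.5 g/kg body weight per day, as in the cases, and both groups are restricted on antibiotics, corticoids, diabetes and bowel disease. So intake is not absent from the comparison, although variation below the limit remains.

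**Bristol score is a doubtful covariate.** Stool consistency may be downstream of GM. Cases also collect stool after starting omega-3 or placebo and, depending on the day, protein or placebo, which controls do not take. This stands: it does not belong in the main model.

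**Conclusion.** The point holds in a limited form. The article plans a matched comparison and names, for its primary GM contrast, methods with no stated use of the matching. If matching is individual and ρ lies between 0.1 and 0.3, tests are conservative (true size 3.9% to 1.9%) and power at 0.35 SD is 71–73% instead of 74–84%. Near ρ = 0, or with frequency matching, the loss is negligible. Residual age or BMI differences act separately and can raise false positives modestly. All these sizes rest on assumed values.

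Stronger readings that the documents do not support:
- *Ignoring the pairs creates false positives.* With positive correlation it does the reverse. Only uncorrected imbalance can inflate them.
- *The whole plan is unadjusted, or GM is compared by an independent-samples t-test.* Adjusted regression is planned for the associations. The t-test is named only for clinical parameters, without saying whether it is paired.
- *Matching will leave too few pairs.* The plan contains no rule for discarding unmatched people.
- *Adjustment would remove confounding.* It would reduce the measured part. Unmeasured factors, and the supplements that only cases take before baseline, would remain.

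This is worth changing because the change is nearly free. It does not undermine an exploratory study.

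**What to change.** 1. Reconcile the Abstract with the Participants section: state whether matching is individual or by frequency, and give the caliper widths.
2. For alpha-diversity, cell counts, taxa and faecal markers, make the primary contrast a regression of a transformed or rank/ordinal outcome on case status, sex, age and BMI, with pair-clustered standard errors where pairs exist. Unpaired participants can stay in.
3. Run PERMANOVA with the same terms and test case status marginally, that is, after the other terms. Restrict permutations within pairs only if every analysed participant belongs to a pair.
4. Put Bristol score and protein and energy intake in sensitivity models only. Add medication only if it is confirmed that the questionnaire records it.
5. Reword the Discussion to say that matching and adjustment reduce bias from sex, age and BMI.

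The cost is revised wording, a few degrees of freedom and slightly more analysis. Items 1 to 3 and the named sensitivity covariates need no new data.
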